**2.5.3. The role of dispatch doctors**

**The role of emergency doctors:**

- Identifying P0 and P1 (call priority) incidents
- Identifying B assessments
- Dealing with requests for inter-hospital transfers
- Dealing with requests from other SAMUs
- Dealing with SMUR requests
- Operations on public roads
- SMUR assessment

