**The role of general practitioners or non-emergency care hospital doctors**

- Identifying P2 incidents
- Responding to requests for medical advice
- Dealing with calls related to continuous outpatient care

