***Experimental conditions***

Salivary cortisol will be collected for each ARM over three working days in three different positions: calls, resource deployment or action, and assessment.

Participants will be notified of proper sampling conditions for the salivary cortisol assay. Once enrolled on the study participants shall undertake not to drink or eat anything for half an hour prior to the sample being collected as well as during the two hours when samples are taken. Subjects must also agree not to smoke thirty minutes prior to samples being taken as well as during the sample collection period. Regarding other variation factors which affect salivary cortisol levels, light levels will not vary over the working day and subjects will be working in a seated position, so standing will not be accounted for.

Calls assays will be taken for will be for the same time period to prevent any bias arising in terms of inter- and intra-individual circadian variations in salivary cortisol levels.

The first incoming call for the ARM shall be used as the reference, however accidental or mistaken calls will be excluded from the study. During the call, a salivary control assay will be taken for the call ARM, with the first assay being marked T0. Additional assays will be conducted for call ARMs every 15 minutes after T0 for 1 hour and 30 minutes, followed by a final assay at two hours after the call, which translates to eight assays which will be used to generate the acute stress curve. Cortisol assays will all be carried out at the same time to prevent nycthemeral variations. Each sample will be taken as soon as the subject ends the call and hangs up the phone.

The same salivary cortisol assay following the same principle will then be carried out on the doctor the call was transferred to. The same assay will also be carried out on the action ARM and the assessment ARM. The next day the salivary cortisol assay will be carried out on the same ARMs but as assigned to different areas.

Three medical dispatch assistants should therefore have salivary cortisol assays administered every day as should a doctor - either an emergency doctor or independent practitioner - based on the severity of the call.

Each additional call will be noted when taking salivary cortisol measurements. Each event over the two hour sampling period will likewise be recorded to prevent any bias arising and for a better understanding and analysis of the curves generated.

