**4.2.4 Other data collected**

Intervening events (such as other calls, specific contexts, etc.) shall be recorded during periods where salivary cortisol assays are being taken (i.e. over 2 hours per each subject).

Furthermore during each call, the gravity of the situation at hand will be assessed using the following classification to look for a correlation between physiological stress levels and the seriousness of the call.

For ARMs:

Three levels of priority shall be applied when transferring the call to a dispatch doctor:

P0: procedural response of an SMUR team being sent followed by priority dispatch

P1: priority dispatch

P2: dispatch that can be put on hold without risk to the patient until other dispatches which are currently out can arrive

For dispatch doctors:

Dispatch doctors make their decisions based on four levels of emergency:

R1: a patent or latent life-threatening emergency requiring a resuscitation team (SMUR) being dispatched.

R2: a real emergency although not life-threatening which would require the attention of a nearby doctor, ambulance or the fire brigade within a period of time contractually agreed to between the dispatcher, the acting party and the caller.

R3: access to continuous care required although the time it takes to do so presents no immediate risk; a medical prescription for later may be suggested.

R4: medical advice or drug prescription can be provided over the phone.

For assessment ARMs:

Three levels of priority are applied by ARMs when forwarding assessments to dispatch doctors:

B0: assessment with signs of distress which were not apparent during the call. This call should be answered as a priority by the emergency dispatch doctor.

B1: assessment providing additional information which was not present during the initial dispatch but absent of any signs of distress or seriousness.

B2: an assessment in line with the data collected during the call to dispatch.

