**8. Statistics**

**8.1. Description of anticipated statistical methods to be used, including a timetable for any anticipated interim analyses**

**Description of sampling**: qualitative variables shall be described as a percentage, using the absolute frequency and a 95% confidence interval, with quantitative variables being described as an average and standard deviation or as medians over a range and with interquartile intervals.

**Description of biological stress**: this shall be described by calculating the difference between cortisol peak(s) observed and cortisol levels measured on the day off (as an average and standard deviation or as medians over a range and with interquartile intervals).

**Description of perceived stress**: the ASA score shall be described as a median and standard deviation.

**For exploratory purposes**: a comparison of the delta peak/cortisol base rate from the three ARM posts using a non-parametric Kruskal Wallis test, with the same being carried out based on ARM seniority, the seriousness of the call and the doctor's status (emergency doctor or independent practitioner); a comparison of the delta peak/cortisol base rate per chronic stress levels (PNOSI questionnaire) and personality (NEO PI-R questionnaire).

The ASA score (perceived stress) shall be compared to the delta peak/cortisol base rate (biological stress) using the Spearmann correlation coefficient.

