**8.2. Planned number of individuals to be included in the study with the statistical grounds for the number given**

This is a study where the main objective is descriptive; additionally it may serve a purpose as a feasibility study with respect to the comparative (secondary) objectives. 20 ARMs and 20 doctors (emergency doctors or independent practitioners) are expected to be included.

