**8.3. Planned degree of statistical significance**

Again, this is a descriptive study. Statistical tests shall be carried out for exploratory purposes with alpha risk set at 5%.

- 1. **Statistical criteria for ending the research**

Not applicable

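### The exploratory test on doctor status cannot be separated from call severity, and the severity objective is given a test that ignores the order of the grades

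*Protocol*

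**What the plan says.** Section 8.1 lists, for exploratory purposes, Kruskal-Wallis comparisons of the delta between peak and base cortisol. The first grouping factor is ARM post, "with the same being carried out based on ARM seniority, the seriousness of the call" and, last in the list, the doctor's status. Each factor is taken on its own. Section 8.3 adds: "Statistical tests shall be carried out for exploratory purposes with alpha risk set at 5"%.

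Several places describe which doctor meets which call:

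- Section 2.5.3 gives emergency doctors the task "Identifying P0 and P1 (call priority) incidents" and general practitioners the task "Identifying P2 incidents".
- Section 4.2.1 repeats this routing: less serious calls go to independent practitioners and the more severe to emergency doctors, who alone can authorise an SMUR dispatch.
- Section 4.2.2 (Experimental conditions) makes it the sampling rule. One doctor is sampled per call, "either an emergency doctor or independent practitioner - based on the severity of the call".
- Sections 4.1 and 4.4 give each doctor two conditions, one call and one day-off witness.

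On severity, section 3.2 states the objective as a correlation with stress, and section 4.2.4 says that gravity is graded in order to look for a correlation. Section 4.2.4 then sets out three scales: P0-P2 for ARMs transferring a call, R1-R4 for doctors ("Dispatch doctors make their decisions based on four levels of emergency") and B0-B2 for assessment ARMs. No mapping links them, and section 8.1 does not say which scale its seriousness test uses.

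**The concern.** A status comparison is informative only if the two kinds of doctor can be compared on similar calls. Here triage assigns the call and the doctor together. A higher delta in emergency doctors could come from graver calls, from the profession, or from both, and the planned test cannot tell which. Section 8.2 says the study may serve as a feasibility study for the comparative objectives, so a triage effect read as a professional difference could be carried into a later design.

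The severity objective has a different problem. The grades are ordered and the objective asks for a correlation, but the assigned test treats the grades as unordered labels. The same section uses Spearman's coefficient for ASA against cortisol. The planned test therefore answers a different question from the one posed and is less sensitive to a steady rise of stress with severity.

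**Working it through.** **1. Overlap of doctor status and severity.**

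| | Emergency doctor | Independent practitioner |
|---|---|---|
| P grades listed (2.5.3) | P0, P1 | P2 |
| Routing (4.2.1) | more severe calls | less serious calls |
| Call conditions per doctor (4.1, 4.4) | 1 | 1 |

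On the P scale, as the roles are listed, no grade appears in both columns. With one call per doctor there is no within-doctor contrast either. Adjusting the status test for P would leave nothing to compare, and splitting doctors into P0/P1 and P2 reproduces the status split. On the R scale some overlap is possible, for example at R2. R1 needs an SMUR team, so it should fall to emergency doctors alone.

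**2. How often the status test would be significant with no status effect.** The protocol gives no effect size, SD or power, so there is no figure to reproduce. Section 8.2 states "20 ARMs and 20 doctors (emergency doctors or independent practitioners) are expected to be included", with no split by status. Assumptions: normal deltas with equal SD, true status effect zero, severity effect d (in SD) carried wholly by status, two-sided alpha 5%.

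Normal approximation for n per group: power ≈ Φ(d·√(n/2) − 1.96). With n = 10, √(10/2) = 2.236:

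- d = 0.5: Φ(1.118 − 1.96) = 20%
- d = 0.8: Φ(1.789 − 1.96) = 43%
- d = 1.0: Φ(2.236 − 1.96) = 61%

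Simulated rejection rates:

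| Test and split | 0.5 SD | 0.8 SD | 1.0 SD |
|---|---|---|---|
| Kruskal-Wallis, 10 v 10 | 19% | 39% | 55% |
| Mann-Whitney, 10 v 10 | 15% | 35% | 52% |
| Kruskal-Wallis, 15 v 5 | 14% | 30% | 42% |

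Repeat runs agree to within one or two points. With d = 0 at 10 v 10 the Kruskal-Wallis rate is about 5%. If half of the emergency doctors' calls were at the practitioners' severity level, the 10 v 10 Kruskal-Wallis rate at 0.8 SD falls from 39% to 13%.

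**3. The three scales side by side.** P grades the priority of transfer, R the response needed, and B what the later report adds to the first call. B2 means that the report agrees with the call, so a grave call confirmed as grave is B2, the lowest B grade. The action post has no scale of its own; the P block is headed for ARMs but concerns transfer to a doctor. A pooled ranking across P, R and B would have no meaning.

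**4. How much severity information there is.** Section 4.2.1 studies the same call at all three ARM posts. 20 ARMs × 3 posts = 60 sessions; at 3 ARMs per call this is 60 / 3 = 20 calls. Within one post, each ARM and each call contribute one session, about 20 in all.

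For scale only, take 20 calls split 7/7/6 over three grades and a linear rise of 0.5 SD per grade. Kruskal-Wallis then rejects about 26% of the time and a Spearman trend about 38%. The split and the linear rise are assumptions; the linear rise favours the trend test.

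**The case against.** The strongest reply is that little hangs on this. The main objective is descriptive, the tests are declared exploratory, doctor status is not among the objectives in section 3, the routing is openly described, and no claim about the profession is planned. That stands and sets the priority, but it does not make the status test interpretable.

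It can also be said that Kruskal-Wallis is valid for ordered groups and that naming a scale is normal content for an analysis plan. Both are fair. What remains is that the protocol itself asks for a correlation and assigns an order-blind test.

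Three stronger readings are tempting and are not supported:

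- **That severity decides which ARM posts are sampled, so that the post comparison is tilted.** Sections 4.2.1 and 4.2.2 sample all three posts on the same call, with three ARMs every day, so index-call severity is balanced across posts as written. That a call settled by telephone advice (R4) gives later posts little work is an inference about exposure and is not a stated sampling rule. The post comparison needs no severity adjustment on this ground.
- **That the protocol pools P, R and B.** It does not say so. Section 4.2.4 sets the scales out by role, and a test within one role is readable.
- **That the cost of ignoring order can be read from a calculation with 60 independent sessions.** The sessions come from about 20 calls and repeat the same ARMs, so such figures do not describe this study.

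**Conclusion.** The concern holds in a limited form. The status test is confounded with call severity by routing, and no later adjustment on the P grade can repair it; only the claim can change. A severity test in doctors on P is the same contrast, and one on R is exposed to the same routing.

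The rates of about 15-19%, 35-39% and 52-56% at 0.5, 0.8 and 1.0 SD are illustrations. They rest on assumed effect sizes, an assumed 10 v 10 split and complete non-overlap, and they shrink with an uneven split or with overlap.

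The mismatch between the correlation objective and Kruskal-Wallis is internal to the protocol and free to correct. Because every test involved is exploratory, the priority is minor.

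**What to change.** In section 8.1:

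- Report doctor status only as a description of emergency doctors on P0/P1 calls against practitioners on P2 calls, with no conclusion about status.
- Test severity against the cortisol delta with an ordered method (Spearman or a trend test), using the index call's P grade for ARMs. Do this within post, or in a model that allows for the shared call and the repeated person.
- Analyse R only in doctors and B only in assessment ARMs, never pooled with P. Keeping B matters because a call graded P2 at transfer can become B0 later. State that any R result in doctors is subject to the same routing confounding.

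The cost is a few sentences in section 8.1. The P grade is already recorded under section 4.2.4, so no new data are needed. The downside is that no separate claim about doctor status can be made.

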**8.2. Planned number of individuals to be included in the study with the statistical grounds for the number given**

This is a study where the main objective is descriptive; additionally it may serve a purpose as a feasibility study with respect to the comparative (secondary) objectives. 20 ARMs and 20 doctors (emergency doctors or independent practitioners) are expected to be included.

**8.3. Planned degree of statistical significance**

Again, this is a descriptive study. Statistical tests shall be carried out for exploratory purposes with alpha risk set at 5%.

- 1. **Statistical criteria for ending the research**

Not applicable

**8.5. Method used to account for missing, unused or non-valid data**

Missing data will not be extrapolated. Subjects for which half or more of data are missing shall be excluded from analysis.

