**Objective measurement of stress: salivary cortisol assay under various experimental conditions.**

4 experimental conditions should be applied to ARMs: "call, action, evaluation, witness"

2 experimental conditions should be applied to doctors: "call, witness"

- Secondary evaluation criteria

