## 4.4. Expected length of individuals' participation

Inclusion period length: 1 month

Length of each individual's participation: four instances of two hours for ARMs and two instances of two hours for doctors.

ARMs: four instances of 8 samples each / Doctors: Two instances of 8 samples each

Total length of the study: 6 months

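### The missing-data rule excludes whole subjects, although the cortisol outcome is computed per work series: it drops dispatch assistants (ARMs) with a usable delta and keeps some with none

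*Protocol*

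**What the plan says.** Protocol section 8.5 has two sentences: "Missing data will not be extrapolated", and "Subjects for which half or more of data are missing shall be excluded from analysis". The unit of exclusion is the subject. The section does not say which data are counted, does not require the day-off series, and sets no minimum for a single curve.

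Section 8.1 describes biological stress by "calculating the difference between cortisol peak(s) observed and cortisol levels measured on the day off", and then compares that delta between the three ARM posts with a Kruskal-Wallis test. The delta is therefore a quantity per work series, and each one also needs the day-off series.

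Section 4.1 states that "4 experimental conditions should be applied to ARMs": three posts and the witness condition, which section 4.2.2 places on a day off. Section 4.4 gives the sample counts: "ARMs: four instances of 8 samples each / Doctors: Two instances of 8 samples each". Nothing elsewhere in the protocol qualifies the rule in section 8.5.

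**The concern.** The rule and the outcome work on different units. A share of all of a subject's data does not show whether any delta can be computed, because one of an ARM's four series (the day off) enters every delta and each of the other three enters only one. A percentage over all four can fail in both directions: it can remove a person with a valid delta and retain a person with none.

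A percentage over the whole subject also says nothing about any one curve. The outcome uses a maximum over eight samples, so a curve with few samples left is not comparable with a full one.

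Section 8.2 plans only 20 ARMs and 20 doctors, so each usable series lost to the rule counts. Some loss is foreseeable: eight swabs in two hours on duty, each soaked for two or three minutes, and a day-off series that participants collect and store themselves.

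**Working it through.** **Inputs.** Series and samples per ARM: sections 4.1 and 4.4. Sampling times: section 4.2.2. Definition of the delta: section 8.1. Threshold: section 8.5, exclusion at 50% missing or more.

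**1. Samples per work series.** T0 gives 1. "Additional assays will be conducted for call ARMs every 15 minutes after T0 for 1 hour and 30 minutes" gives 6 (15, 30, 45, 60, 75 and 90 minutes). The two-hour sample gives 1. Total 1 + 6 + 1 = 8, which agrees with "which translates to eight assays which will be used to generate the acute stress curve".

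**2. Denominator.** An ARM has 4 × 8 = 32 samples, so exclusion starts at 16 missing.

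**3. All whole-series patterns for an ARM (2⁴ = 16).** A delta exists if the day off and at least one work series are present.

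| Work series present | Day off | Patterns | Missing | Rule | Any delta? |
| --- | --- | --- | --- | --- | --- |
| 3 | yes | 1 | 0/32 = 0% | kept | yes |
| 2 | yes | 3 | 8/32 = 25% | kept | yes |
| 1 | yes | 3 | 16/32 = 50% | excluded | **yes** |
| 0 | yes | 1 | 24/32 = 75% | excluded | no |
| 3 | no | 1 | 8/32 = 25% | kept | **no** |
| 2 | no | 3 | 16/32 = 50% | excluded | no |
| 1 | no | 3 | 24/32 = 75% | excluded | no |
| 0 | no | 1 | 32/32 = 100% | excluded | no |

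Four patterns are misclassified: three wrongly discarded and one wrongly kept. An ARM without any day-off sample can lose seven more samples and still be kept: 15/32 = 46.9%.

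**4. Does the count depend on what data means?** Section 4.2.3 attaches one ASA rating to each cortisol sample. Counting both gives 16/64 = 25% and 32/64 = 50%, so the result is the same.

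**5. Completeness of one curve.** A work series cut to a single sample, with all else complete, is 7/32 = 21.9% missing, and the ARM is kept.

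**6. Effect on the work peak.** The maximum of a subset cannot exceed the maximum of the full set. If m of 8 samples are lost at random, the chance that the peak sample is among them is m/8: 12.5% for m = 1, 25% for m = 2, 50% for m = 4 and 87.5% for m = 7.

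The protocol gives no cortisol mean or SD, so the size of the shift needs an assumption. Two were simulated, with 200,000 curves each:

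- Flat curve, independent noise: mean shift in the maximum of −0.07 SD (m = 1), −0.16 (m = 2), −0.39 (m = 4) and −1.42 (m = 7).
- Baseline of 5 units, a rise of 3 to 5 units peaking at 20 minutes, noise SD 1 to 2: −0.11 to −0.20 units (m = 1), −0.23 to −0.43 (m = 2), −0.61 to −1.11 (m = 4) and −2.24 to −4.04 (m = 7). The mean full-series peak above baseline was 3.49 to 6.13 units.

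**The case against.** **The rule does not say that data means samples.** This is right, and it matters for the wrongly discarded ARMs. If PNOSI and NEO PI-R each count as one item, the ARM with one post and a day off is 32/66 = 48.5% missing and is kept; one more lost sample with its ASA rating makes 34/66 = 51.5% and exclusion. If each of the 180 NEO PI-R questions counts, the total is 64 + 1 + 180 = 245, and losing every sample and rating is 64/245 = 26%. The rule would then never act on lost samples alone, the wrongful discards would largely disappear, and the wrongful retention would be worse. The result therefore rests on counting cortisol, or cortisol plus ASA.

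**Keeping an ARM without a day off produces no false number.** This also stands. Nothing is imputed, so that ARM simply has no delta. The main objective covers perceived stress too, and the work samples and ASA ratings stay usable. The harm is an analysis set that does not match the outcome.

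**The downward pull comes from using a maximum, and curve-level detail usually belongs in the analysis plan.** The first half is true. But section 8.5 itself fixes the exclusion rule, and fixes it at a level that cannot control the loss within a curve.

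**Two stronger readings are not supported.** A reader might infer that doctors are mishandled as well, since a doctor without a day off is 8/16 = 50% missing and excluded. That doctor has no computable delta, so the rule gets this case right. A reader might also infer that the comparison of posts is pushed toward no difference or reversed, because busy posts would lose more swabs. Section 4.2.1 calls the call post the most stressful but says nothing on sample loss. Section 8.1 does not say how the eight day-off values become a reference, so losses there could move the delta either way.

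**Conclusion.** The point holds for ARMs. With cortisol (or cortisol plus ASA) as the data counted, the rule misclassifies 4 of 16 whole-series patterns: it discards a computable delta at exactly 50% missing and keeps an ARM with none at 25%. It also allows a work series of one sample in a subject only 21.9% incomplete.

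The sign of the effect on the work peak is certain: equal or lower. Its size depends on assumed curves; it is small for one or two lost samples and large when most of a curve is gone. The net effect on the delta, and on the comparison between posts, is not established.

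Sections 8.2 and 8.3 make the study descriptive with exploratory tests, so the consequence is moderate: avoidable loss of usable series and an unclear analysis set in a small study. The rule should be changed, but the study does not fail on it.

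**What to change.** Replace the subject-level rule in section 8.5 with a series-level one:

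- Analyse a post's delta if the day-off reference is available and the work series meets a minimum completeness fixed in advance, for example at most one or two of the eight samples missing and the samples around the expected cortisol peak present.
- Otherwise leave that series out of the delta analysis only, and keep the subject's other valid series and ASA scores.
- State that, for this rule, data means cortisol samples.

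Requiring the day-off reference and one valid work series removes all four mismatches. Under the curves assumed above, a limit of two missing samples holds the mean shift in the peak to about −0.16 SD (flat curve) or −0.23 to −0.43 units (curve with a rise).

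The cost is a few sentences in section 8.5 and no new data. The downside is that the number of subjects will differ between posts and between outcomes, so it must be reported for each.
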